#### Sample size and recruitment

In a bilateral situation, a *P* value of <0.0166 will be considered clinically and statistically significant after Bonferroni adjustment for multiple testing, to ensure an overall bilateral alpha risk of 5%. To detect the minimal clinically significant difference (at least 10 points, with a standard deviation of 11 points), with a bilateral alpha risk of 0.0166 and a power of 80%, 54 patients per group are required. Interim analysis to evaluate the primary hypothesis is planned when half the patients have been included and have at least 2 months of follow-up. This interim analysis will be performed according to the rules established by O’Brien and Fleming (Alpha Spending Function with bounds calculated by O’Brien’s method) [24].

The calculation of the sample size takes into account the specificity of the randomization by the Zelen design, and the primary end point of quality of life measured with a multidomain questionnaire: Two groups of equal size, constituted by random assignment; one group will receive standard therapy, and the other group will receive the experimental therapy, or standard therapy if the patients refuses to consent to experimental therapy. The heterogeneity of the intervention group will increase the variance of the difference (Δ_z_) between groups for the primary end point, as compared with classic randomization (Δ_c_), albeit without introducing a measurement bias. The increase in variance will increase with the percentage (Φ) of subjects who receive standard treatment in the intervention group, with [25].

In these conditions, the number of subjects must be multiplied by (1/(1 - Φ)^2^). For the ALIM-K study, we estimate that the percentage (Φ) of subjects who receive standard treatment in the intervention group will be low (estimated at around 10% by experts). Quality of life, as measured by the questionnaire, will yield a score for each domain. To take into account the multiplicity of comparisons, the Bonferroni correction will be applied to the alpha risk.A variation in quality-of-life score of at least 10 points (on a scale of 0 to 100) will be considered as clinically significant.

At an alpha risk of 0.0166, power of 80%, and a percentage Φ of 10%, the number of subjects required to detect a difference of at least 10 points (±11) in quality-of-life score is at least 70 per group (54 × 1.25), or 140 patients in total.

We thus plan to include 16 patients in each of the 10 participating centers ( eight in each group in each center. Participating centres are all specialist cancer institutes, with a high recruitment potential for this type of (relatively frequent) patient profile. Indeed, a preliminary survey performed for the purposes of prior grant applications suggested that more than 20 such cases per year are treated in participating centers. Based on these recruitment estimates with an anticipated moderate inclusion rate, the inclusion period is scheduled to last 30 months, and the total duration of the study including setup, data collection, and analysis will be 42 months.

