## Methods/design

### Participants, interventions, and outcomes

#### Study setting

This study will be conducted nationwide in France in nine comprehensive cancer centers selected for their expertise, and qualified to treat patients with more-advanced cancers, as well as in two university teaching hospitals (University Hospital of Besançon and Henri Mondor Hospital, Creteil, France).

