### Assignment of interventions

The study will comprise two arms: one intervention group (parenteral nutrition group) and one control group (oral feeding group). The Zelen single-consent design requires that consent be obtained only from the intervention group, for their participation in a study involving initiation of parenteral nutrition. The patient will be informed of the study requirements (inclusion criteria, aims, composition, expected effects and benefits, foreseeable risks, contraindications and so on) to allow them to decide whether to consent to participate. The information delivered to the patient will not mention randomization. Patients allocated to the oral feeding group will be informed about their management, and will consent only to completion of the quality-of-life questionnaire. Patients randomized to the intervention group may refuse to consent to the intervention, in which case, they will be included in the control group.

The distribution of patients between the study arms will be performed by the investigator during the first consultation to verify eligibility criteria, by means of Internet access to a 1-to-1 randomization list, balanced by center, and generated automatically by using SAS software (version 9.3; SAS Institute Inc., Cary, NC, USA) and administered by the Clinical Investigation Centre of the University Hospital of Besancon, France.

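### The stated sample size inputs require 27 patients per group (54 in total), not 54 per group, so either the sample size or the standard deviation is misstated

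*Protocol article*

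**What the plan says.** Under Sample size and recruitment, the protocol article gives every input to a two-group comparison of means. The difference is "at least 10 points, with a standard deviation of 11 points", and the Bonferroni-adjusted level is chosen "to ensure an overall bilateral alpha risk of 5"%. It concludes that, "with a bilateral alpha risk of 0.0166 and a power of 80%, 54 patients per group are required".

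It then allows for patients in the intervention arm who refuse and receive standard care. The rule is to multiply by 1/(1 − Φ)², with Φ put at about 10%, and the result "is at least 70 per group (54 × 1.25), or 140 patients in total".

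The recruitment paragraph continues: "We thus plan to include 16 patients in each of the 10 participating centers", eight per group. An interim analysis is planned once half the patients have been included and have two months of follow-up. Study setting places the trial "in nine comprehensive cancer centers selected for their expertise" plus two university teaching hospitals.

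Allocation uses a "1-to-1 randomization list, balanced by center". The primary comparison in the Primary objective section is an ANOVA on two-month scores.

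**The concern.** A standardised difference of 10/11 = 0.91 is large, and 54 per group is far more than 80% power needs for it, even at a level of 0.0166. The stated figure is exactly twice the t-test answer.

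This calculation is the only justification the article gives for the size of the trial, and its two possible explanations point in opposite directions. If SD 11 is what the investigators believe, the number to be randomized is about double what the stated power requires, in a population the Discussion itself calls particularly vulnerable. If a larger SD was used, the number may be about right, but the printed SD is wrong and the real margin is much thinner than SD 11 suggests. A reader cannot tell which of these holds.

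**Working it through.** **Inputs** (Sample size and recruitment; allocation from Assignment of interventions): difference δ = 10; SD σ = 11; two-sided α = 0.0166; power 80%; 1:1 allocation; Φ = 0.10.

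**1. Size per group, normal approximation.** n = 2(z₁₋α/₂ + z₁₋β)²(σ/δ)² = 2 × (2.395 + 0.842)² × (1.1)² = 25.4, so 26 per group.

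**2. Size per group, t-test.** Solving the noncentral t for 80% power gives n = 26.8, so 27 per group. Power is 78.5% at 26 and 80.3% at 27. The total over both groups is 2 × 27 = 54.

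**3. Attempt to reproduce 54 per group.** With the normal formula, δ = 10 and σ = 11, varying α (0.05, 0.05/3, 0.0166, 0.0166/2, 0.0166/3, 0.05/9, 0.005) and sidedness at 80% power gives 15 to 33 per group. At two-sided 0.0166, 54 per group appears only when power is set to 99%. By t-test, power at 54 per group is 98.8%.

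**4. What would make 54 per group right at 80% power (t-test).** An SD of about 15.8 (16.1 by the normal formula) with δ = 10, or a difference of about 6.9 points with SD 11.

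**5. Refusal factor.** 1/(1 − 0.10)² = 1/0.81 = 1.235; the article uses 1.25.

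| Starting n per group | × 1.235 | × 1.25 | Article |
|---|---|---|---|
| 54 | 66.7 → 67 | 67.5 → 68 | at least 70 |
| 27 | 33.3 → 34 | 33.75 → 34 | – |

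The requirement on the stated inputs is therefore 34 per group, 68 in total. As a cross-check, refusal by 10% dilutes the difference to 0.9 × 10 = 9 points. At 34 per group, power for 9 points with SD 11 is 81.7%.

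**6. Power at the planned sizes, SD 11, two-sided α 0.0166, all patients evaluable (t-test).**

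| n per group | Power for 10 points | Power for 9 points |
|---|---|---|
| 54 | 98.8% | 96.4% |
| 70 | 99.8% | 99.2% |
| 80 | 99.95% | 99.7% |

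**7. Interim analysis.** One O'Brien-Fleming look adds about 1%: 27 × 1.008/0.81 = 33.6, still 34 per group.

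**8. Recruitment.** 16 × 10 = 160, which is 20 above 140. Half of the target is 70 or 80 patients, depending on which applies. Study setting lists 9 + 2 = 11 sites, while the recruitment paragraph and Trial status give 10.

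**The case against.** The best defence of 54 per group is a change score. The Primary objective section also plans an ANOVA on the variation between day 1 and day 60. If 11 is the SD at one time point and the two measurements are uncorrelated, the SD of the change is 11 × √2 = 15.6, and the t-test needs 53 per group. That is close to 54 but not equal to it, and no such assumption is written. The article attaches SD 11 directly to the 10-point difference and names two-month scores for the primary comparison. This does not rescue the figure, but it does mean the cause cannot be settled from the text.

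Four stronger readings are tempting and not supported.

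- *The trial is underpowered.* On the stated inputs the reverse holds.
- *54 is certainly the two-arm total relabelled.* The exact factor of two suggests it, but an SD near 15.8 explains the figure as well.
- *The later totals contradict one another.* Twice 70 is 140; 70 is a rounding up of 67 or 68 under the words at least; and 160 exceeds a stated minimum. The step to 160 is unexplained, but neither it nor the 1.25 makes the 80% wrong. The center count is a separate editorial mismatch with no effect on power.
- *Half of the randomized patients are surplus.* That treats everyone as evaluable. Deaths and missing scores could use up part of the excess, although no allowance for them is stated.

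**Conclusion.** The point stands on the mismatch between 54 and 27. The printed inputs give 27 per group before the refusal factor and 34 per group (68 in total) after it; the article states 54 and 70 (140 in total). At the stated sizes, power is about 99% rather than 80%, provided that SD 11 is right, refusal is 10%, and all 70 per group are evaluable. If instead 54 per group is right at 80% power, the SD must be about 15.8. One of the two figures is misstated, and the article does not show which. This must be corrected because the printed justification of the trial's size is off by a factor of two on its own terms. The remaining items (1.25 for 1.235, 140 against 160, 10 centers against 11) are minor and do not cause the error.

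**What to change.** Rewrite the Sample size and recruitment section; no patients need be added.

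1. State whether 54 is a total or a per-group figure, or which SD was actually used and where it comes from. The SD should come from the original calculation or a source, not be solved backwards from the existing sample size.
2. Restate sample size and power consistently. On SD 11 that means 27 per group before and 34 per group after the refusal factor.
3. If 140 is kept on SD 11, give the reason, for example an explicit allowance for deaths and missing scores, and report power for the number expected to be evaluable. The 99.2% applies only if all 70 per group contribute.
4. Replace 1.25 by 1.235 and show the rounding (54 × 1.235 = 67, if 54 per group stands).
5. Explain the step from 140 to 160, so that the interim analysis at half the patients refers to one target.
6. Reconcile the 10 centers with the nine plus two in Study setting.

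The cost is one recalculation and a text correction.

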### Statistical analysis

All analyses will be performed on an intention-to-treat basis. A formal statistical analysis plan will be prepared before the database lock. Any deviation from the statistical analysis plan will be detailed and discussed in the study report.

Clinical and sociodemographic variables collected at baseline will be described as mean ± standard deviation (SD) for normally distributed continuous variables, the median (interquartile) range for nonnormally distributed variables and number (percentage) for qualitative variables. The number of health-related quality-of-life questionnaires completed at each measurement point will be reported.

#### Primary objective

A treatment group will be considered as superior to the other if at least one of the three domains of the primary end point (physical function, overall health status/quality of life, or fatigue) of the QLQ-C15-PAL questionnaire is clinically and statistically significantly better, without any clinically and statistically significant deterioration in at least one of the other two domains.

Comparison of the three domains of the QLQ-C15-PAL questionnaire (between the parenteral nutrition and oral feeding groups) will be performed on an intention-to-treat basis for all patients randomized and included, by using ANOVA on scores at 2 months. Analyses will be adjusted for the presence (or not) of palliative chemotherapy. The variation in the score for each domain between inclusion (day 1) and day 60 will be compared with ANOVA, taking into account stratification variables and potential confounding factors, such as center, type of cancer, and patient characteristics.

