### Hypotheses and objectives

In view of the uncertainty regarding the risk/benefit ratio of supplemental parenteral nutrition, we aim to investigate which of two management options (initiation of supplemental parenteral nutrition or no introduction of parenteral nutrition) proves to be superior in terms of health-related quality of life without a significant decrease in survival, in the palliative phase of cancer.

The primary objective of the ALIM-K study is to evaluate the clinical benefit in terms of health-related quality of life, as evaluated at 2 months (or at treatment discontinuation for patients who discontinue treatment allocation before 2 months), by using the European Organisation for Research and Treatment of Cancer (EORTC) Quality of Life Questionnaire Core 15 Palliative (QLQ-C15-PAL), and in particular, the physical function, global health, and fatigue subscales [13], of the initiation of supplemental parenteral nutrition as compared with no parenteral nutrition, in malnourished cancer patients at the palliative stage who have a functional digestive tract, and in the absence of any curative therapy.

Secondary objectives are to compare the effects of both types of nutrition on overall survival and nutritional parameters.

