**Secondary outcomes** Secondary end points are as follows: ➢ Overall survival, defined as the time from the date of randomization until death of any cause. Patients who are still alive at the end of the study will be counted at the date of last follow-up.➢ Other (non-primary-end point) domains of the QLQ-C15-PAL questionnaire (pain, emotional function, nausea/vomiting, appetite, dyspnea, constipation, and sleep) at 2 months (or at treatment discontinuation for patients who discontinue allocated treatment before).➢ Longitudinal analysis of all domains of the QLQ-C15-PAL.➢ Nutritional parameters: weight, C-reactive protein (CRP), prealbumin, albuminemia.➢ For patients at the end-of-life stage: the Quality of Life at End of Life (QUAL-E) questionnaire will be administered by a clinical research assistant and completed based on the patient’s responses. This questionnaire has been validated in the English-language version [22], and a cross-cultural validation into the French language has been completed [23]. The French-language version comprises 25 questions (compared with 24 in the English version) plus one global question, covering five domains:

life completionrelationships with the health care systempreparation/anticipatory concernssymptom impactconnectedness and affective social support

The five possible response modalities for each item are coded from 1 to 5. The score for each domain is calculated by summing the responses for each item. The global QUAL-E score is the sum of all 26 items. Linear transformation yields score values ranging from 0 (lowest quality of life) to 100 (highest quality of life). The scores from the individual domains of the QUAL-E will also be analyzed.

In the “parenteral nutrition” group, the following information will be recorded: ➢ Quantity and duration of treatment actually administered.➢ Biologic results from blood samples taken more than 4 hours after the end of infusion of the last bag of mixture, including blood gases, evaluation of phosphorus, magnesium and calcium levels, hepatic enzymes and triglycerides, and evaluation of glycosuria and ketonuria.➢ Any and all adverse effects.

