#### *Time schedule for participants (see Table* 2*)*

**Table 2 Tab2:** **A schematic diagram of time schedule for enrolment, interventions, assessments, and visits for participants**

	Pre-randomization (day -7 to day 0): Check inclusion and exclusion criteria					
	Zelen's randomization					
	Parenteral nutrition group			Oral feeding group		
	Present "parenteral nutrition" info			Present "oral feeding" info		
	Day 1	Days 2-60*	Day 61-death**	Day 1	Days 2-60*	Day 61-death**
Obtain informed consent	X			X		
Record demographic data	X			X		
Take medical history	X			X		
*Treatment*						
Concomitant treatments	X	X		X	X	
Specific treatment (prior or ongoing)	X	X		X	X	
*Patient status*						
WHO Status	X	X	X	X	X	X
Karnofsky index	X	X		X	X	
Estimated life expectancy	X			X		
*Anthropometric data*						
Height	X			X		
Weight	X	X	X	X	X	X
*Biology*						
Lactic acid dehydrogenase	X			X		
C-reactive protein, albumin, prealbumin	X	X		X	X	
Blood count, electrolytes (including phosphorus, calcium, magnesium)	X	X				
Hepatic enzymes (AST, ALT, PAL, Gamma GT, Bilirubin)	X	X				
Triglycerides	X	X				
Ketonuria, glycosuria	X	X				
Quality of life questionnaires (QLQ-C15-PAL and QUAL-E***)	X	X	X	X	X	X
Socio-economic variables	X			X		
Dietetics consultation	X			X		
Ingesta questionnaire		X	X		X	X
Evaluation of metastatic disease		X			X	
Intervention supportive care		X			X	

*Follow-up consultation at least once per month **Evaluation once per month. ***Administer the QUAL-E if the patients consider themselves to be at the end of life (definition at the discretion of the physician and patient).

*Day -7 to day 0:* Patients who meet the inclusion criteria will be identified from medical files or from regular staff meetings or multidisciplinary case reviews, by the oncologist or the treating physician from palliative care. Once identified, eligible patients will be randomized through a dedicated website, and will be allocated to either the “parenteral nutrition” or the “oral feeding” group. After randomization, the patient will be given the appropriate patient-information leaflet for the allocated group, after oral information has been provided to the patient.

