*Day 1:* The informed consent form, duly signed by the patient and the investigator, will be retrieved by a clinical research assistant. A first consultation will take place at this time to perform standard clinical evaluation and, in particular, to identify and manage any factors that might potentially promote anorexia and digestive disorders. Performance status will be evaluated by using the Karnofsky score, demographic and socioeconomic data will be recorded, and a complete nutritional evaluation, including CRP, albumin, and prealbumin will be performed in all patients. Patients allocated to the parenteral nutrition group will also undergo biological tests before initiation of nutrition. A consultation with a dietitian will be held for all patients. No systematic dietetic follow-up is planned for the study; the cadence of the follow-up consultations is left to the discretion of the relevant healthcare professionals in accordance with their standard practice.

Last, each patient will complete the QLQ-C15-PAL, and patients who are aware of the palliative status of their disease will also complete the QUAL-E.

*From day 1 to day 60:* Patients will have regular follow-up consultations during the follow-up period; at least once per month, based on the patient’s planned attendance at the hospital (for oncology consultations or scheduled admission). The Karnofsky index, quality-of-life evaluation, and details of energy intake will be recorded at each consultation. Nutritional parameters (weight, CRP, prealbumin, albumin) will also be recorded for all patients. Adverse effects will be reported, and serious adverse events will be declared to the relevant pharmacovigilance authorities in the University Hospital of Besancon, France. For patients in the parenteral nutrition group, quantity and duration of nutrition actually administered will be recorded, and complete biological evaluation will be performed (including blood gases, evaluation of phosphorus, magnesium and calcium levels, hepatic enzymes and triglycerides, and evaluation of glycosuria and ketonuria).

Beyond 2 months of treatment, discontinuation or not of parenteral nutrition will be left to the physician’s discretion.

*From day 61 until death*: Quality of life, energy intake, weight, and performance status by using the Karnofsky index will be recorded once per month. Any serious adverse events will be declared to the relevant pharmacovigilance authorities.

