#### Change in quality of life over time

Quality-of-life scores will be generated according to algorithms described in the EORTC scoring manual. The mechanism of missing scores will be studied and classified according to the methods of Diggle [26] and Rubin [27] (that is, MCAR (Missing Completely At Random), MAR (Missing At Random), and MNAR (Missing Not At Random). The mechanism of missing data will be determined by comparing patients with no missing scores with those with at least one missing score at baseline, according to baseline characteristics of patients. If required, more detailed patterns will be defined. If missing data are MNAR, multiple imputations may be performed. Otherwise, simple imputation by the mean will be retained.

The time to quality-of-life score deterioration (TTD) will be defined as a modality of longitudinal quality-of-life analysis and will be defined as the time from inclusion in the study to a first deterioration, with a minimum clinically significant difference of at least 5 points as compared with the baseline score, or death of any cause, whichever occurs first [28, 29]. Although three domains of the EORTC QLQ-C15-PAL are being targeted for the primary end point, scores from all domains of the questionnaire will be studied as secondary analyses. The TTD curves will be calculated by using the Kaplan-Meier method and described, by using median and 95% confidence interval (CI). TTD curves will be compared according to treatment group by using the log-rank test and univariate Hazard Ratio with 95% CI. A multivariate Cox regression model will then be performed to investigate potential prognostic factors of TTD. All variables collected at baseline will be tested by univariate analysis. Variables with a *P* value ≤0.20 by univariate analysis will be eligible for inclusion in the multivariate Cox analysis.

Mixed-model analyses of variance for repeated measures will also be performed to test a time effect, a treatment effect, and an interaction between time and treatment. If missing data are not completely at random, a pattern-mixture model will be used.

Analysis of the secondary end points will focus first on comparison of overall survival. Overall survival is defined as the time from study registration to death of any cause. Patients who are lost to follow-up will be counted at the date of their last follow-up.

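### The superiority rule omits the survival condition in the trial's own hypothesis, and overall survival is given two start points, one of them undefined

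*Protocol article*

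**What the plan says.** All references are to the protocol article.

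- **Aim.** Hypotheses and objectives opens by asking which management option "proves to be superior in terms of health-related quality of life without a significant decrease in survival". The same section then states a primary objective in terms of QLQ-C15-PAL alone and adds: "Secondary objectives are to compare the effects of both types of nutrition on overall survival and nutritional parameters".
- **Decision rule.** Primary objective, under Statistical analysis, says: "A treatment group will be considered as superior to the other if at least one of the three domains" is better to a clinically and statistically significant degree, "without any clinically and statistically significant deterioration in at least one of the other two domains". Survival does not appear.
- **Survival analysis.** Change in quality of life over time puts overall survival first among the secondary end points, with a log-rank test and Cox hazard ratios. No sentence connects the result to the superiority conclusion.
- **Start of overall survival.** Outcomes has "Overall survival, defined as the time from the date of randomization until death of any cause". Change in quality of life over time has "Overall survival is defined as the time from study registration to death of any cause". Study registration is not defined.
- **Order of events.** Under the Zelen design, allocation precedes information and consent: "After randomization, the patient will be given the appropriate patient-information leaflet for the allocated group". On day 1, "The informed consent form, duly signed by the patient and the investigator, will be retrieved by a clinical research assistant". Primary objective equates inclusion with day 1.

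**The concern.** The rule is complete as written and uses the same word, superior, as the hypothesis, but with a weaker meaning. This is a conflict between two statements in the article, not a detail left to an analysis plan. A trial following the rule to the letter could announce a winner that its own hypothesis rules out.

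Death also carries no weight inside the rule. The primary score is taken at 2 months, or at treatment discontinuation if that comes first. A patient who dies before 2 months without a discontinuation assessment has no score, and nothing in the rule counts that death against the arm. Losing the frailest patients could then make an arm's remaining scores look better. The survival condition in the hypothesis is the natural guard against this.

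The start date matters more here than in a conventional trial, because patients are allocated before they are informed and what they are then told differs by arm. A time zero placed after that step is no longer protected by randomization.

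**Working it through.** **1. Hypothesis against rule**

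| Result for one arm | Hypothesis | Rule under Primary objective |
|---|---|---|
| One domain better, no other domain worse, survival not significantly worse | Superior | Superior |
| One domain better, another significantly worse | Not addressed by domain | Not superior |
| One domain better, no other domain worse, survival significantly worse | Not superior | Superior |

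The third row is the conflict. It follows from the text and needs no figure.

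**2. What a no-significant-decrease condition can and cannot show**

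The article gives no number of deaths and no survival margin, so there is no figure of the plan's to reproduce. Inputs: 140 patients (Sample size and recruitment); follow-up until death (Time schedule for participants); 1:1 allocation. Assumptions: 100 to 140 deaths, with 140 meaning that every patient dies, and a two-sided 5% test.

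Standard error of the log hazard ratio: SE = 2/√D.
Upper 95% limit when the observed hazard ratio is 1.0: exp(1.96 × 2/√D).
Power against a true hazard ratio of 1.3: 1 − Φ(1.96 − ln(1.3) × √D/2), with ln(1.3) = 0.262.

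| Deaths D | SE | Upper limit at HR 1.0 | Power, true HR 1.3 | Chance of a non-significant result |
|---|---|---|---|---|
| 100 | 0.200 | 1.48 | 26% | 74% |
| 120 | 0.183 | 1.43 | 30% | 70% |
| 140 | 0.169 | 1.39 | 34% | 66% |

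The hazard ratio detectable with 80% power is exp((1.96 + 0.84) × 2/√D), which is 1.75 at 100 deaths and 1.61 at 140. The condition would stop a claim when the survival harm is large. It would usually not stop one when the harm is modest.

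**3. Could a confidence-limit margin replace it?**

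To exclude a hazard ratio of 1.3 with 80% power when the true ratio is 1.0 takes 4 × (1.96 + 0.84)²/(ln 1.3)² = 4 × 7.84/0.0688 ≈ 456 deaths. That is more than three times the 140 patients planned.

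**4. The two start points**

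- If registration means entry on the randomization website, the two definitions give the same date and only the wording differs.
- If registration means inclusion or consent on day 1, time zero falls after allocation. A patient who dies between allocation and day 1 could drop out of the survival analysis, although Statistical analysis commits all analyses to intention to treat.

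The article does not say which is meant. It does treat randomization and inclusion as separate steps, since the primary comparison covers patients both randomized and included.

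**The case against.** The strongest reply is that the rule sits under the heading Primary objective and matches the formal primary objective, which is quality of life only, with survival secondary. Survival is not neglected: it comes first among the secondary analyses, with a log-rank test and a hazard ratio. This stands to the extent that the gap lies between the opening hypothesis and the rule, not in the survival analysis. It does not remove the conflict over what superior means.

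Four stronger readings are tempting, and the article does not support them.

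- **That only patients alive at 2 months contribute a primary score.** Outcomes also accepts a score at treatment discontinuation, so some patients who die earlier will contribute. Death also counts as an event in time to deterioration, and a pattern-mixture model is foreseen, though both are outside the superiority rule. The gap concerns patients who die with no discontinuation assessment.
- **That the two survival origins differ by up to a week.** Table 2 labels day −7 to day 0 as before randomization, whereas the text below it puts randomization inside that window. Assignment of interventions places allocation at the first consultation to check eligibility, and Information and consent gives information on the day of the first consultation. The gap is unclear, may be zero, and is not shown to differ by arm.
- **That time to deterioration should also start at randomization.** It is measured against a baseline score taken on day 1, so a start at inclusion is coherent.
- **That the rule should require the confidence interval to exclude harm.** The article sets no margin, and one that excludes modest harm is out of reach with 140 patients, as step 3 shows.

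**Conclusion.** The point holds in two parts.

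First, the superiority rule leaves out a condition that the hypothesis states, so an arm with significantly shorter survival could be declared superior. This rests on the text alone.

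Second, overall survival has two differently worded start points, and one is undefined. Whether any patient's survival time would change depends on what registration means. The risk to intention to treat exists only if it means a step after allocation.

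Restoring the condition makes the rule agree with the hypothesis but does not show that survival is unharmed. Under the assumed 100 to 140 deaths, identical observed survival would still be compatible with a hazard ratio of about 1.39 to 1.48, and a true ratio of 1.3 would go undetected in 66% to 74% of such trials. The article should say so, in case a non-significant test is read as reassurance. Both corrections should be made because they change what may be concluded and cost almost nothing.

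**What to change.** 1. Under Primary objective, add that a group is not declared superior if its overall survival, measured from randomization, is significantly worse than that of the other group.
2. State that the survival hazard ratio and its 95% confidence interval will be reported beside any superiority claim, and that a non-significant log-rank test will not be presented as evidence of no harm.
3. Under Change in quality of life over time, replace study registration with randomization, so that overall survival has the same origin as under Outcomes.

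Leave the origin of time to deterioration as it is.

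The cost is wording. Survival is already collected and analysed, and the sample size need not change. The superiority claim becomes slightly harder to make: if survival is truly equal and the test is two-sided at 5% (an assumption, since the article sets no level for survival), a given arm would be blocked by chance in 0.05/2 = 2.5% of trials.
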